### Development and testing of the digital information tool (Digi-Do)

As a pre-phase, a pilot study was performed for the development and testing of the digital information tool (Digi-Do), approved by the Regional Ethics Committee (Dnr 917-17) with 30 patients in total (15 women with breast cancer and 15 men with prostate cancer). The Digi-Do tool was developed through a co-design process, where patients and staff were involved in all design steps; initial exploration of work, discovery process and prototyping [37]. According to the study’s co-design, iterative methodology [38 in manuscript], changes have since been made to the digital information tool and a second version has now been developed for the full RCT. The present study has been approved by the Swedish Ethical Review Authority (Dnr 2020-00170). An ongoing systematic literature review will also guide the present study, and the project is registered in PROSPERO (PROSPERO; 168073).

The digital information tool applied in this project is divided into two separate but coherent applications (apps) for mobile devices: one (VR-app) with a guided tour of the RT-department with a voice-over to describe 360 images to create a sense of actually having visited the department prior to start of RT, and one (information app) containing information obtained through the pre-treatment phase. If a VR-effect is not desirable, the patient can complete the simulated study-visit on their mobile phone or tablet as well as present the images in the browser of an integrated media player. Three areas of information are available in the information app: (1) Q&As from the existing written information, presented both in writing and a recorded voice; (2) practical information, such as maps, public transportation options with relevant links to public transport, telephone numbers, and information about possibilities for staying at the patient hotel; and (3) three short animated films about cancer and physical activity during RT.

### Data collection

Socio-demographic data concerning age, marital status, number of persons in household, level of education, working/retired/sick leave, stage of disease, co-morbidities, and treatment will be gathered from the patients and/or their medical charts. The instruments for data collection will be administrated in person or by post at the baseline collection, and by post (including a pre-paid return envelope) on consecutive collections (Table 1). Two reminders will be sent for each data collection, separated two weeks in time if necessary. Data will be coded and manually entered in SPSS. The SPSS database will be stored on a secure digital storage (JU share files) at Jönköping University.

**Table 1 Tab1:** Data collections at different points in time

Point in time	Data collections
Baseline	Socio-demographic and co-morbidity data Distress (DIS-A); Self-efficacy (GSES); Health literacy (functional, communicative & critical, e-HLQ) Notebook written by 30 patients
Week of commencing RT treatment	Distress (DIS-A) Notebook collected and returned after reading
Within a month of completion of RT treatment	In depth/or telephone interviews with participants
Six months post-completion of RT treatment	Distress (DIS-A); Self-efficacy (GSES); Health literacy (functional, communicative & critical, e-HLQ) Telephone interviews with participants

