## Background

Among women, breast cancer is the most diagnosed cancer and the leading cause of cancer death worldwide [1]. In 2019, the Swedish national cancer register recorded 9225 cases of breast cancer; 9157 women and 68 men (0.7%). The incidence rate of breast cancer in Sweden is expected to continue to rise, due to an increase in both the general and ageing population numbers [2]. Radiation Therapy (RT) is a common treatment (received by 75–80% of breast cancer patients) after surgery and is a complex process based on the use of high energy X-rays to eradicate cancer cells, important in reducing the risk of local recurrence [1]. While the RT procedure itself takes only a few minutes and is painless, it requires meticulous preparation and patients then need to attend the RT treatment centre 5 days a week for up to 3–5 weeks. Moreover, in Sweden, the waiting time is often quite long, sometimes up to 10 weeks [2]. The high-tech environment and unfamiliar nature of RT can affect the patient’s experience of the treatment [3–5]. Furthermore, misconceptions or a lack of knowledge about RT processes can increase their levels of anxiety and enhance feelings of being unprepared at the beginning of treatment [6–8].

Having received correct information about future treatment may enable patients to realistically assess advantages and disadvantages as well as foresee possible treatment results. This may in turn create a feeling of increased knowledge and security as well as reduce distress for the patient [9–13]. A number of Swedish acts state that the healthcare system must provide each patient with individually tailored information and the opportunity to choose between different treatments [14–16] or stipulate that healthcare providers should actively ensure that the information has been received and understood by the patient [10]. Having a person-centred approach to information provision and communication means to enhance shared decision making, seeing the person as a capable individual who wants to adapt generic information to his or her social context and experiences [17, 18].

When informing patients, their health literacy must also be considered, i.e., their ability to acquire, understand, and use information about their health, including that related to cognitive and social functions [19]. Health literacy can be seen as being dynamic, and hence can fluctuate, depending on the state of the individual, the situation, the culture, or the environment [20].

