### Sample

Adult patients (> 18 years) diagnosed with breast cancer, stage I–II, who are not receiving adjuvant or neo-adjuvant chemotherapy or anti-Her-2 treatment and with RT as additional treatment after surgery, will be consecutively included during the planned post-operative visit to the surgical clinic. They will also need the ability to read, write, and understand Swedish to adhere to the digital information tool and the data collection instruments, and have access to a smartphone or a tablet. Patients responding to these inclusion criteria will be consecutively asked to participate at the post-surgery follow-up visit and receive information (oral and written) about the study. After providing their signed informed consent, participants will be randomized to either the intervention group (A) or the control group (B) by drawing a note (marked with group A or B) for each participant from a black box. Randomization will be stratified by hospital, and a total of 80 participants will be finally included at each hospital (40 in each group). The participants in the intervention group will receive oral and written information regarding the digital information tool.

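### A posted baseline form can be completed after allocation, and reminder-prompted replies to the RT-start distress form can fall outside the week they are meant to describe

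*Protocol article*

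**What the plan says.** The Sample section of the protocol article sets the order of events at the post-operative visit: "After providing their signed informed consent, participants will be randomized to either the intervention group (A) or the control group (B) by drawing a note". It then adds: "The participants in the intervention group will receive oral and written information regarding the digital information tool". Consent is the only condition named for the draw.

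On the questionnaires, the Data collection section states: "The instruments for data collection will be administrated in person or by post at the baseline collection". All later collections go by post. It continues: "Two reminders will be sent for each data collection, separated two weeks in time if necessary". That rule covers every collection, so it includes baseline and the RT-start form.

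Table 1 places the second distress measurement (DIS-A) in the week RT begins. The Background says of RT that "patients then need to attend the RT treatment centre 5 days a week for up to 3–5 weeks", and that the wait for it can reach 10 weeks.

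The hypothesis in the section on sample size compares the groups six months after RT. The Quantitative data section compares the groups at every time point and also plans generalized linear models for repeated measures.

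**The concern.** A baseline should describe patients before allocation can have affected them. Here a form sent home is answered by someone who, on the stated order, may already have drawn a note and, in the intervention group, may have opened the apps. The wait for RT is when the tool is meant to be used, so the return period for a posted baseline overlaps the exposure period. If the tool lowers distress, such forms lower the intervention group's baseline and pull any analysis that uses baseline toward no effect. Knowing the allocation could shift answers even without use of the tool, in a direction that cannot be predicted.

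This reaches beyond distress. Self-efficacy and the health literacy scales, including the eHLQ, are collected only at baseline and six months, so baseline is half of their data. The eHLQ concerns how people deal with digital health services, and being handed an app could plausibly change those answers.

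The RT-start form is the only distress measurement between baseline and six months. It alone serves the part of the primary aim that concerns distress during RT. A reply given weeks into treatment describes a different state from the first days, and mixing the two blurs that comparison.

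**Working it through.** The plan gives no figure for this point, so there is nothing to reproduce. The check is calendar arithmetic followed by a simple bias formula.

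**1. RT-start form.** Inputs from the article: two reminders, two weeks apart; RT of up to 3–5 weeks. Assumptions: the form is posted when RT starts; the first reminder goes out at week f; completion and return take t = 0 to 1 week. The reply to the second reminder then arrives at week f + 2 + t.

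| First reminder | Reply to second reminder | Share of a 3-week course | 4-week course | 5-week course |
|---|---|---|---|---|
| f = 0 (most favourable) | weeks 2–3 | 67–100% | 50–75% | 40–60% |
| f = 2 | weeks 4–5 | 133–167% | 100–125% | 80–100% |

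For example, 4/3 = 133%, 4/4 = 100% and 4/5 = 80%. Even the favourable row lies outside the week named in Table 1. The basic conflict does not depend on f: replies prompted by two reminders two weeks apart cannot both fall within one named week.

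**2. Baseline form.** By the same reckoning, a posted baseline answered after the second reminder returns 2–3 weeks after posting (f = 0) or 4–5 weeks after (f = 2). Both lie within a wait of up to 10 weeks.

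**3. Effect on estimates.** Let d be the true effect, p the share of the intervention group that completes baseline after exposure, g the fraction of the effect already present at that moment, and b the slope on baseline in an adjusted analysis.

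- Shift in the intervention group's baseline: p × g × d
- Change-score estimate: d − p × g × d, a loss of p × g
- Baseline-adjusted estimate: d − b × p × g × d, a loss of b × p × g

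The article gives none of p, g or b. With b = 0.5 assumed:

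| p | Change score, g = 1 | Adjusted, g = 1 | Change score, g = 0.5 | Adjusted, g = 0.5 |
|---|---|---|---|---|
| 10% | 10% | 5% | 5% | 2.5% |
| 25% | 25% | 12.5% | 12.5% | 6.25% |
| 50% | 50% | 25% | 25% | 12.5% |

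To put this on a scale, 63 per group with 85% power at a two-sided 0.05 (sidedness assumed) corresponds to (1.960 + 1.036) × √(2/63) = 0.53 SD. With g = 1 and p = 10%, 25% and 50%, that effect would be estimated as 0.48, 0.40 and 0.27 SD by change score, and as 0.50, 0.46 and 0.40 SD with baseline adjustment.

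**4. Which analyses use these forms.** A direct comparison of the groups at six months uses neither form. A repeated-measures model that includes baseline, or any change or baseline-adjusted analysis, uses the baseline form. The group comparison at the start of RT uses the RT-start form.

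**The case against.** The strongest reply is that this reads fault into a condensed article. Nowhere does it say that baseline follows the draw, nor when the apps become available. In-person baselines may well be finished before the note is drawn. Details of sequence and return windows often sit in a full protocol that is not shown. This stands as a limit: the text permits the problem but does not show that it happens, or how often. It does not remove the point, which rests on rules the article does state: a postal option for baseline, reminders at every collection, and a draw conditioned on consent alone.

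A reader might infer that the primary result is biased. The documents do not support that. The hypothesis is a between-group difference six months after RT, and an unadjusted comparison at that point is untouched. The article names neither a change score nor a baseline-adjusted analysis; the repeated-measures models are the planned analyses that are exposed.

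A reader might also infer that the RT-start form is in effect an end-of-treatment measurement. That is too strong. It could hold only for patients who answer after the second reminder, and mainly if the first goes out at two weeks. The article gives the spacing, not the starting date. The 3–5 weeks is also a general Background statement rather than a schedule for this trial.

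Finally, setting late forms to missing would not be a clean remedy. Late responders may differ in distress, and a mixed model would then rely on a missing-at-random assumption.

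**Conclusion.** The point holds as an inexpensive improvement, not as a flaw in the six-month contrast. The stated procedures allow a baseline that is given after allocation and possibly after exposure, and they allow RT-start scores from weeks 2–3 or, on the slower reading, weeks 4–5.

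The size of any bias cannot be determined from the article. The range of 10–50% of the effect lost by a change score, and 5–25% by a baseline-adjusted estimate, rests on an assumed share of 10–50%, an assumed slope of 0.5 and the full effect being present when the form is filled in. With a partial early effect the losses shrink in proportion. If all baselines are in fact completed before the draw, the baseline part disappears.

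**What to change.** - **Baseline:** have the form completed at the post-operative visit before the note is drawn. Where it has to be posted, draw the note and release the tool only once it has come back.
- **RT-start distress form:** hand it out at the RT department in the first treatment week. Patients attend five days a week, and the notebooks are already due from participants that week.
- **All forms:** record the date of completion. Keep late forms and analyse them by actual date, or examine them in a sensitivity analysis, rather than setting them to missing automatically.

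The cost is a few minutes at the surgical visit, some handling of forms at the RT department, and a short delay to the draw for any posted baseline. That delay also postpones access to the tool within the waiting period and may need one further contact, which is a reason to prefer completion at the visit.

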#### Primary outcome measure

*DIS-A. The NCCN Distress Thermometer* is a brief screening tool for cancer patients to assess psychosocial distress [39], including 34 dichotomous items on the presence of physical, emotional, family, practical, and spiritual problems. A score of 4.5 or higher indicates the patient is distressed and in need of support. The Swedish translation of the DT/PL is consistent with the original English version [40].

#### Secondary outcome measure

*The General Self-efficacy Scale* [41]*, validated into Swedish GSES* [42] is an instrument that asks the persons´ opinion about how he or she can deal with difficulties and challenges in life. It consists of 10 items (eg. “I can always manage to solve difficult problems if I try hard enough”, “I am confident that I could deal efficiently with unexpected events” and “I can usually handle whatever comes my way”) rated on a four-point Likert scale (“not at all true” to “exactly true”), summarized across respondents (range 10–40); higher scores indicate higher self-efficacy.

*The communicative and critical health literacy scale*—*Swedish version*: This instrument consists of five items self-rated on a five-point Likert scale, ranging from “not at all” to “precisely”. The first three items include statements focusing on the capacity for collecting, extracting, and understanding relevant health information. The other two items include statements highlighting capacities to judge the reliability of the information and to apply health information to everyday life. In this study we have added an open-ended question concerning information sources [43, 44].

*The Swedish Functional Health Literacy scale:* This scale comprises five items about persons’ skills in reading and understanding health information. The items can be self-assessed on a five-point Likert scale ranging from ‘never’ to ‘often’. In this study, we have excluded two of the original questions (difficulty reading health information and time to read health information) as these were found to be less relevant in relation to our aim, and we added one open-ended question concerning how to remember information relating to health, illness, and treatment [44].

*The eHealth Literacy Questionnaire (eHLQ)* is a psychometrically robust multidimensional tool designed to be used to understand and evaluate people’s interaction with digital health services [45]. The eHLQ consists of 7 scales capturing various attributes of the users and the intersection between users and technologies. The applied Swedish version of the eHLQ (translated from English) is currently undergoing validation testing (the results will be published during 2020).

*The Self-Administered Comorbidity Questionnaire:* The Swedish version of this scale has been modified from the English version, and is a method to assess comorbidity for clinical and health services research [46].

#### Time measurements and field notes

Ten patients respectively from groups A and B will, during the planned post-operative visit to the surgical clinic, be consequently asked to participate in the time measurement and observational part of the study (*n* = 20). Three of the planned treatments for the first week of RT, and, additionally, one session in the last week of treatment, will be measured based on seven timepoints; patient enters door of RT room, patient lies on table, first image, first field beam on, last field beam on, patient leaves table, and patient leaves RT room. During each RT session, questions asked by patients and staff will be documented as field notes, including what subjects are addressed, who initiates the question, and whether, how, and to where the staff refers the patient for further information. These field notes will be taken into account for validation of the content of the information in the app, but not further analysed.

#### Notebook and in-depth interviews

Approximately 30 patients (in group A) will be strategically asked to participate in the qualitative part of the study. The patients will be asked to make notes in a notebook during the waiting period prior to the start of RT as well as during the RT treatment period. The participants will be encouraged to write reflections with a focus on the support, guidance, and information they receive from healthcare professionals, relatives, and the digital information tool in these notebooks. In the first week of RT treatment, patients will submit their diaries to the researchers. The text in the notebooks will be read and summarized to support the development of in-depth questions for upcoming individual interviews. These individual in-depth and/or telephone interviews will take place on two occasions (1–4 weeks and 6 months post-RT completion) and with at least ten of the patients who have accepted participation and have made regular notes. Questions will include topics such as their experiences of receiving the information through the digital information tool during the waiting time and treatment period, of using the digital information tool, to what extent the digital information has affected their involvement and preparedness for the radiation treatment, as well as their experiences during the time since the end of RT.

### Data analysis

#### Quantitative data

Data will be analysed descriptively taking the level of scale into consideration, i.e., using mean (m) and standard deviation (SD) when relevant, or, otherwise, median (md) and range. Group comparison at each point in time will be completed using relevant parametric or non-parametric methods [47]. *P *values < 0.05 will be considered statistically significant. Generalized linear models [47] will be used to analyse differences between groups and for repeated measures over time for the continuous variables, while nominal (categorical) variables will be tested with chi-square test (exact).

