#### Sample size and hypothesis

The Distress Thermometer will be used as the primary outcome measure and used as a basis for the power calculation. A sample size of 63 persons in each group (a total of *n* = 126) would give an 85% power to detect a 0.10 improvement in the intervention group at an alpha = 0.05.

The null hypothesis is that there is no difference in distress between the intervention group and the control group; the alternative hypothesis is that the intervention group will experience 10% lower distress than the control group at the follow-up, six months post-completion of RT. The anticipated recruitment rate is 4.4 participants per site and month.

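### The stated group comparisons use neither the baseline scores nor the hospital stratum, and the plan does not say which analysis tests the six-month hypothesis: valid tests, but precision given away for nothing

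*Protocol article*

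**What the plan says.** The section Quantitative data names two routes for continuous outcomes. The first is a comparison of the groups at each time: "Group comparison at each point in time will be completed using relevant parametric or non-parametric methods". The second is generalized linear models, which "will be used to analyse differences between groups and for repeated measures over time for the continuous variables". The threshold is that P "values < 0.05 will be considered statistically significant". No covariate is named for either route, and no correlation structure, random effect or robust variance is named for the models.

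Three other places bear on this:

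- Sample size and hypothesis puts the alternative hypothesis at one time: "the intervention group will experience 10% lower distress than the control group at the follow-up, six months post-completion of RT".
- Table 1 (Data collection) lists "Distress (DIS-A); Self-efficacy (GSES); Health literacy (functional, communicative & critical, e-HLQ") at baseline and again at six months after radiotherapy. Distress is also measured in the week radiotherapy starts. Distress therefore has three occasions and the other outcomes two.
- The section Sample states: "Randomization will be stratified by hospital". There are two hospitals, with 40 patients per group at each.

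**The concern.** A two-group test at a single time uses one score per patient. It takes no account of the patient's own baseline score, which the trial already collects, or of the hospital by which patients were randomised. If baseline and later distress are correlated, part of the spread in the six-month scores is predictable and need not count as noise.

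Three further points follow from the wording:

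- Table 1 has a column for point in time, and its first row is baseline. Read plainly, a comparison at each point in time includes a significance test before the intervention, where randomised groups can differ only by chance.
- A generalized linear model in its basic form assumes independent observations, so a reader cannot tell how two or three scores from one patient will be handled.
- The two routes can give different P values for the same hypothesis, and the plan does not say which one decides.

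At stake are power for the primary hypothesis and freedom from a choice of test made after the data are seen.

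**Working it through.** **Reference point from the plan.** The article states "A sample size of 63 persons in each group", which "would give an 85% power to detect a 0.10 improvement in the intervention group at an alpha = 0.05". Read as a standardised difference, 0.10 would need 2 × ((1.960 + 1.036)/0.10)² = 1796 per arm (two-sided), so 63 does not follow on that reading. That is a separate matter. Here 63 per arm serves only as an anchor: the standardised difference it detects with 85% two-sided power is √(2/63) × (1.960 + 1.036) = 0.534.

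**Gain from baseline.** Adjusting for a baseline score with correlation r to the six-month score multiplies the variance of the group difference by 1 − r². The article gives no r, so a range is assumed. Effective n is 63/(1 − r²). Power at the anchor is Φ(2.996/√(1 − r²) − 1.960) for 63 per arm, and the last column repeats this for the planned 80 per arm with no dropout.

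| r (assumed) | 1 − r² | Variance cut | 63 per arm act like | Power, 63 per arm | Power, 80 per arm |
|---|---|---|---|---|---|
| 0 | 1.00 | 0% | 63 | 85.0% | 92.2% |
| 0.3 | 0.91 | 9% | 69 | 88.1% | 94.3% |
| 0.5 | 0.75 | 25% | 84 | 93.3% | 97.4% |
| 0.7 | 0.51 | 49% | 124 | 98.7% | 99.7% |

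The variance cut depends only on r. The power columns also depend on the anchor effect of 0.534, which the article does not state.

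**Gain from hospital.** If hospital explains a share s of the outcome variance, leaving it out of a test after stratified randomisation inflates the standard error by 1/√(1 − s). For s = 1%, 5% and 10% (assumed) this is 0.5%, 2.6% and 5.4%. Type I error becomes 0.049, 0.044 and 0.039, slightly conservative.

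**Standard errors of the per-time tests.** Each uses one value per patient, so within-patient correlation does not enter. Simulated type I error for a single-time test was 0.050.

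**Standard errors of the generalized linear model, if it were fitted to independent rows.** The article does not say this will be done; the case is worked to see what it would affect. Take within-patient correlation ρ = 0.5 (assumed), equal variances and m occasions.

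- Group effect averaged over occasions: the true variance is 1 + (m − 1)ρ times the model's. Type I error is 2(1 − Φ(1.96/√1.5)) = 0.110 for m = 2 and 2(1 − Φ(1.96/√2.0)) = 0.166 for m = 3. This is anti-conservative.
- Group-by-time: the true variance is 1 − ρ times the model's, so the standard error is overstated by 1/√0.5 = 1.41. Type I error is 2(1 − Φ(1.96/√0.5)) = 0.006. This is conservative.
- Group contrast at six months from a group-by-time model: the estimate is the raw difference in six-month means and its model variance is 2σ²/n, which is correct when variances are equal. Simulated type I error was 0.048 to 0.053 for two or three occasions at 63 or 80 per arm.

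The article's hypothesis is the third of these contrasts, so even this reading does not inflate its false-positive rate.

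**The case against.** A reader might infer from the model's name that within-patient correlation will be ignored and the standard errors will be wrong. The article does not support this. It says the models are for repeated measures, never states independence, and uses a label that can loosely cover GEE-type fits. The 11% and 17% error rates belong to an averaged group effect under an assumed fit, not to the six-month contrast. This part of the objection stands in full.

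A second objection is that baseline is not discarded, because a repeated-measures model over all occasions contains it. This stands only in part. In such a model the group-by-time contrast from baseline to six months is a difference in change scores, with variance factor 2(1 − r): 1.4, 1.0 and 0.6 at r = 0.3, 0.5 and 0.7. The factors with baseline adjustment are 0.91, 0.75 and 0.51. The per-time tests do not use baseline at all.

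A third objection is that a condensed article may leave covariates and covariance structure to an analysis plan that is not shown. That is fair for the structure of the model, and nothing in the text excludes baseline or hospital. But the article does commit to per-time two-group comparisons, and that stated method can be improved whatever another document adds.

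It is also true that the correlation is unknown, that the trial aims for 80 rather than 63 per arm, that hospital matters little, and that a baseline test biases no effect estimate.

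**Conclusion.** The point holds as a matter of precision and clarity, not of validity. The stated per-time comparisons are valid but use neither baseline nor hospital, and the plan does not name the analysis that decides the six-month hypothesis. Baseline adjustment would cut variance by 9% to 49% for an assumed correlation of 0.3 to 0.7. Any non-zero correlation gives some gain, apart from a negligible cost in degrees of freedom. The hospital term adds little. Any power gain in percentage points depends on an effect size and a correlation that the article does not give, so the table above is illustrative.

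How correlation is handled is an ambiguity to be cleared up. Standard errors would be wrong only under an independent-rows fit that the article does not describe. With equal variances, the six-month contrast would keep about 5% type I error even then.

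**What to change.** State in Quantitative data that:

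- The primary analysis is the group contrast at six months, with its 95% confidence interval, from a linear mixed model for repeated measures (or GEE with robust variance) on the post-baseline Distress Thermometer scores. The terms are group, time, group-by-time, baseline score and hospital, and within-patient correlation is modelled explicitly.
- Self-efficacy and health literacy, which have one follow-up each, are analysed by ANCOVA with the outcome's own baseline and hospital.
- Comparisons at other times are secondary, and baseline is described without a between-group significance test.

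The cost is a change of wording in the analysis plan. The models are available in SPSS, which the trial already uses for its database, and no further data are needed. The change should be made before outcome data are compared by group.
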